Patients will be divided into two groups based on their medical history: (i) Group A: SMuRF-less patients, (ii) Group B: Patients with SMuRFs, defined as those who fulfilled at least one of the following criteria: (i) known history of hypertension and/or antihypertensive treatment prior to AMI, (ii) self-reported use of tobacco products on a systematic basis for up to 12 months before AMI, (iii) history of diabetes mellitus type 1 or 2 and/or treatment with antidiabetic tablets or insulin before AMI or diagnosis of diabetes mellitus based on HbA1c during AMI hospitalization, (iv) known hypercholesterolemia (total cholesterol > 200 mg/dl / LDLc > 150 mg/dl) or treatment with statins or PCSK9is, before AMI. SMuRF-less patients (Group A) are defined as those suffering an AMI in the absence of these comorbidities.

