### Data collection and study procedures

After obtaining written informed consent, the following clinical characteristics will be recorded for each patient: demographics, socioeconomic parameters, complete medical history and medication, prior diagnostic and therapeutic interventions. A self-reported measurement of patients’ physical activity will be provided using the International Physical Activity Questionnaire (IPAQ), which will be completed by each patient before discharge. IPAQ is a validated questionnaire utilized to objectively measure and stratify physical activity by dividing populations into three levels: low, moderate and high physical activity [13]. Obesity will be diagnosed by categorization of body mass index (BMI; Kg/m2) measured before echocardiographic study. Recorded socioeconomic parameters will include education, marital status, employment, income, migration background and ethnicity. Moreover, the 36-item short form (SF-36) standardized questionnaire will be administered to obtain a self-reported measure of their health-related perception of quality of life before the AMI. In addition, patient laboratory data will be recorded on admission and during hospitalization. These include total blood count, standard biochemistry parameters, coagulation tests, thyroid hormone and thyroid-stimulating hormone levels, HbA1c, NTproBNP and HsTnT levels on admission, peak values of HsTnT, and NTproBNP. Moreover, levels of LP(a), apolipoproteins B and A1 (ApoB and ApoA1) interleukin-6 (IL-6) and soluble urokinase plasminogen activator receptor (suPAR) on admission will be assessed. Additionally, coronary angiographic images of every patient will be evaluated by two experienced independent interventional cardiologists blinded as to the demographic and clinical patient characteristics. Angiographic parameters such as lesion characteristics, coronary dominance and the SYNTAX score will be calculated.

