Baseline patient characteristics of each group will be examined and compared using the chi-square test for categorical variables and the 2-sided Student’s t-test for continuous variables or non-parametric tests (Wilcoxon, Mann-Whitney U etc.), when assumptions of normality are not met. Categorical variables will be represented by frequencies and percentages (%) and continuous variables will be summarized by mean ± standard deviation (SD) or median (1st -3rd quartile), as appropriate. In terms of statistical tests recruited for outcomes calculation, the two groups of patients will be compared to each other to identify clinical, laboratory and imaging biomarkers associated with a higher or lower probability of developing a SMuRF-less AMI. The chi-square test will be used to compare the prevalence of clinical parameters among patients with and without SMuRFs, and the t-test and Mann-Whitney U test will be utilized to compare the mean levels of laboratory and imaging biomarkers between the two groups. As mentioned before, univariate linear and logistic regression analyses will be applied to calculate univariate odds ratios, and then multivariate regression analyses will be performed. Finally, in order to identify the optimal combination of epidemiological, clinical, laboratory and imaging biomarkers associated with SMuRF-less AMIs, supervised machine learning algorithms will be used. The resulting clinical-laboratory prediction models will be evaluated with Receiver Operating Characteristic (ROC) curves.

A time-to-event analysis will be performed to assess whether the absence of SMuRFs is associated with better or worse clinical prognosis of patients (secondary outcome). Event rates will be compared by the long-rank test. Μultivariable Cox proportional hazard models will be utilized to adjust the results for clinically relevant and univariately significant variables. The 2-tailed p value of 0.05 will be considered the significance threshold for all statistical tests. All outcomes will be reported with 95% confidence intervals. Data management and statistical analyses will be conducted using SPSS software, version 26 (IBM SPSS Statistics) and R version 3.4.4 (R Foundation for Statistical Computing, Vienna, Austria).

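### Prior drug treatment is part of the Group B definition, so whole-group biomarker comparisons confound SMuRF-less status with treatment, and no stated analysis separates the two

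*Protocol article*

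**What the plan says.** **Grouping (Methods, Study design and population).** Any one of four criteria puts a patient in Group B, and three of them can be met through treatment: "known history of hypertension and/or antihypertensive treatment prior to AMI"; "treatment with antidiabetic tablets or insulin before AMI"; and "treatment with statins or PCSK9is, before AMI". The lipid criterion can also be met without treatment, by known raised cholesterol (total above 200 mg/dl or LDLc above 150 mg/dl). Group A is what remains: "SMuRF-less patients (Group A) are defined as those suffering an AMI in the absence of these comorbidities".

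**Measurement (Data collection and study procedures).** "levels of LP(a), apolipoproteins B and A1 (ApoB and ApoA1) interleukin-6 (IL-6) and soluble urokinase plasminogen activator receptor (suPAR) on admission will be assessed". The same section records "complete medical history and medication", so prior treatment will be in the data. Myocardial work indices are derived from LV strain together with peak systolic LV pressure.

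**Analysis (Statistical analysis).** For the two whole groups, "the t-test and Mann-Whitney U test will be utilized to compare the mean levels of laboratory and imaging biomarkers between the two groups". Univariate logistic models of SMuRF-less status follow, then a multivariable model holding univariably significant and clinically relevant variables, then machine-learning models. Prior treatment is not named as a covariate, stratum or restriction.

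**Interpretation (Discussion and Limitations).** The Discussion considers that imaging differences could be a consequence of the infarction. The Limitations name the observational design, the Greek population, the age limit and the restricted set of biomarkers. Neither mentions prior treatment.

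**The concern.** Treatment is built into the grouping rule. For the named drug classes, Group A has 0% prior use and Group B has some unknown share above that. A marker that treatment lowers will look higher in Group A even if the two groups are biologically identical; a marker that is truly higher in Group B can be masked.

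This affects what the study presents as new. The Discussion offers Lp(a), ApoB, ApoA1, IL-6 and suPAR as biomarkers not previously examined in this population, and hopes to move from them to predictors and a risk-stratification tool. The whole-group tests and univariate models cannot tell a treatment difference from a difference in SMuRF-less status. Because univariable significance is one route into the multivariable model, a spurious result at the first step also carries forward.

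**Working it through.** **Inputs from the article.** 75 SMuRF-less patients at 15% prevalence: 75 / 0.15 = 500 in total, which reproduces the stated total, and leaves 500 − 75 = 425 in Group B. Two-sided threshold 0.05.

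**Inputs assumed, because the article does not give them.** Equal underlying ApoB in both groups, mean 100 and SD 25; a share p of Group B on lipid-lowering treatment, 15% to 35%; a proportional reduction r in those treated, 20% to 40%.

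**Formulas.**
- Spurious difference: D = 100·p·r
- Group B variance (mixture, same SD within each part): V = 25² + p(1−p)(100r)²
- SE = √(25²/75 + V/425)
- Chance of p < 0.05 = Φ(D/SE − 1.96) + Φ(−D/SE − 1.96)

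| p | r | D | V | SE | D/SE | False significance |
|---|---|---|---|---|---|---|
| 0.15 | 0.20 | 3.0 | 676 | 3.15 | 0.95 | 16% |
| 0.25 | 0.30 | 7.5 | 794 | 3.19 | 2.35 | 65% |
| 0.35 | 0.40 | 14.0 | 989 | 3.27 | 4.29 | 99% |

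Letting the SD shrink in proportion in treated patients moves the middle row to 66%. Simulations of that row gave roughly 56% to 63%.

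**The same check in SD units.** With 75 against 425, a difference of 1.96 × √(1/75 + 1/425) = 0.245 SD is significant. If 30% of Group B are treated and the drug effect is 1 SD, the mean shift is 0.3 × 1 = 0.30 SD: 67% false significance by normal approximation, and 61% (t-test) or 59% (Mann-Whitney) by simulation. If 20% are treated and the effect is 0.25 SD, the shift is 0.05 SD and the figure is only about 7%. The problem is specific to markers that treatment moves appreciably.

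**Does adjustment work?** No Group A patient is on the drug, so a logistic model with treatment as a covariate shows quasi-complete separation, and the treatment coefficient diverges (about −25, SE about 49,000 in one fit with 30% treated and a 1 SD effect). The biomarker coefficient does not diverge. Treated patients stop contributing to it, and it equals the coefficient from the untreated-only fit (difference about 1e-11). At the middle row of the table, with no true difference, rejection rates for ApoB over 1,000 simulated studies were:
- logistic model without treatment: 63%
- logistic model with treatment as a covariate: 4.7%
- logistic model restricted to untreated patients: 4.7%
- linear model of ApoB on group and treatment: 5.9%

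**What restriction costs in precision.** Removing 15%, 25% or 35% of Group B leaves about 361, 319 or 276 patients. The ratio √(1/75 + 1/n) / √(1/75 + 1/425) is 1.013, 1.025 or 1.040, because the 75 Group A patients dominate the standard error.

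**What restriction leaves behind.** Untreated Group B still holds known, untreated hypercholesterolaemia, which Group A excludes. If 10% to 30% of untreated Group B have ApoB 25 units higher (assumed), the group difference is 25 × 0.10 = 2.5 to 25 × 0.30 = 7.5 units in the other direction, with about 12% to 63% false significance.

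**The case against.** **Regression adjustment.** A reader might infer that the confounding cannot be removed by regression, since treatment never occurs in Group A. That is not so: only the treatment coefficient is inestimable, and the biomarker coefficient is the untreated-only estimate. The article's clinically relevant covariates could include prior medication, and covariate lists are commonly left to the analysis plan. This objection stands for the multivariable model. It does not reach the two-group tests or the univariate models, which the article does specify and which are unadjusted.

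**The untreated comparison as the main analysis.** It is tempting to base every claim on Group A against untreated Group B. The group definition does not support that. Known hypercholesterolaemia or hypertension qualifies for Group B without treatment, so the restricted contrast is biased the other way for lipid and pressure-dependent markers.

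**Size of the drug effects.** Nothing in the article says how much any drug class changes any marker. A reader might assume that Lp(a) and IL-6 are distorted as much as ApoB; the documents give no basis for that. The objection limits the size of the point, not its logic.

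**Scope and intent.** The criteria name tablets, insulin, statins and PCSK9 inhibitors; other lipid-lowering or injectable antidiabetic drugs are not in themselves criteria and could occur in Group A. Nor does the article commit to reading differences as biology: it aims to characterise a phenotype, defers predictive value to larger studies, and disclaims causality. But it also hopes to illuminate aetiology, and a purely descriptive reader would still need to know that the contrast is partly treated against untreated.

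**Conclusion.** The confounding follows from the article's own group definition and does not depend on any outside figure: for the named drug classes, Group A is untreated and Group B is a mix, and the stated whole-group tests and univariate models do not separate the two. Its size does depend on assumptions. For ApoB, under the ranges shown, the spurious difference is 3 to 14 units and false significance about 16% to 99%; for a marker only weakly affected it stays near the nominal 5%. The point is most plausible for ApoB and the lipid panel and unproven for Lp(a) and IL-6. It would go too far to say that the models cannot be repaired, or that drug effects are certain to be reported as SMuRF-less biology. This is an inexpensive improvement to the analysis wording and does not show the design to be unsound.

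**What to change.** - For ApoB, ApoA1, Lp(a), IL-6 and the lipid panel, keep the full comparison and add a prespecified comparison of Group A with Group B patients not on a statin or PCSK9 inhibitor before the infarction.
- In the regression, restrict in the same way or enter prior treatment as a covariate. Both give the same biomarker coefficient; do not interpret the treatment coefficient.
- For myocardial work indices, do the same with antihypertensive treatment.
- For ApoB and lipids, also show the comparison without Group B patients who qualify by hypercholesterolaemia.
- Claim an association with SMuRF-less status only when the full and untreated comparisons agree in direction. Otherwise report the difference as possibly due to treatment.
- Add prior treatment to the Limitations.

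**Cost.** Analysis wording only, because medication is already recorded. The standard error of the restricted comparison rises about 1-4% if 15-35% of Group B are treated. Untreated Group B is a selected subset that still includes known untreated hypercholesterolaemia or hypertension, so it must be shown beside the full comparison and not in place of it. The further lipid comparison removes more patients, by a number the article does not allow one to estimate.

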The aim of this study is, therefore, to investigate potential clinical and/or laboratory characteristics associated with SMuRF-less AMIs by comparing the prevalence of clinical parameters and levels of laboratory and imaging indicators among patients with and without SMuRFs. The ultimate goal is the development of a predictive risk stratification model capable of recognizing patients without SMuRFs at high risk for AMI. Secondarily, the study aims at investigating differences in the prognosis of SMuRF-less patients compared to those with SMuRFs.

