A complete and comprehensive transthoracic echocardiographic assessment (TTE) will be performed within 24 hours from admission. All TTE studies will be conducted by certified sonographers/cardiologists using high-end scanners (e.g. Vivid E95, GE Healthcare, Chicago, IL, USA). All analyses will be separately performed by two dedicated expert cardiologists, blinded to the clinical data of all participants. All cardiac chamber sizing quantification, two-dimensional (2-D) and Doppler measurements will be performed in accordance with current recommendations [14, 15]. Simpson’s biplane method will be employed for the calculation of left ventricular ejection fraction (LVEF) for the left ventricle (LV) and abnormal values of conventional LV diastolic parameters will be determined based on recently published criteria [15]. LV diastolic function parameters include mitral inflow and annular velocities and the derived trans-mitral to averaged septal and lateral annular early diastolic velocity ratio (E/e’). All right ventricular (RV) systolic function parameters including tricuspid annular plane systolic excursion (TAPSE), fractional area change (FAC), systolic movement of the RV lateral wall using tissue Doppler imaging (S’), pulmonary artery systolic pressure (PASP) will be evaluated as per current guidelines [16].

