Regarding imaging biomarkers, the innovation of the study lies in the fact that it recruits conventional and novel echocardiographic parameters and analytical angiographic assessment to unravel differences among SMuRF-less patients compared to patients with SMuRFs. As novel imaging modalities have proved, plaque vulnerability and rupture electromechanical complications are not always directly associated with systematically assessed biomarkers and risk factors such as dyslipidaemia [43, 44]. Moreover, an observational study by Figtree et al. indicated differences in the prevalence of left main and left anterior descending culprit lesions in SMuRF-less patients compared to those with SMuRFs [27]. As explained by the authors, this may be partly attributed to the family history of premature CAD and is an important finding potentially leading to a more adverse AMI risk profile in SMuRF-less patients. A potential criticism that our study could deal with is that differences in imaging parameters between patients with and without SMuRFs are likely to be the consequence of AMI rather than a predictive parameter. However, the main objective of the study is to identify associations of clinical, laboratory and imaging variables with SMuRF-less status which should be tested in future larger trials for their predictive value. Thus, the elaboration of additional biomarkers, such as imaging parameters, could contribute to the characterization of the clinical profile of SMuRF-less patients hospitalized with AMI, and shed light on the etiology of this emerging clinical entity. Finally, this study aims to provide data on the prognosis of SMuRF-less AMIs and evaluate emerging evidence highlighting the worse clinical course of these patients [3, 5, 6, 45–49]. The reason behind this observation could be correlated with increased time-to-reperfusion time due to reduced suspicion of AMI in these individuals, but also with undiscovered pathogenetic mechanisms and ‘‘hidden’’ comorbidities which might increase their cardiovascular risk.

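### The planned prediction models mix in variables measured during the infarct and classify SMuRF-less status among AMI patients, so their ROC curves cannot support the stated goal of recognising AMI risk beforehand

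*Protocol article*

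**What the plan says.** **Goal.** The Background states: "The ultimate goal is the development of a predictive risk stratification model capable of recognizing patients without SMuRFs at high risk for AMI". The opening of the Discussion repeats the aim of ending with a risk-stratification tool.

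**Analysis.** The Statistical analysis section describes the final modelling step as follows: "identify the optimal combination of epidemiological, clinical, laboratory and imaging biomarkers associated with SMuRF-less AMIs, supervised machine learning algorithms will be used". The next sentence reads: "The resulting clinical-laboratory prediction models will be evaluated with Receiver Operating Characteristic (ROC) curves". The same section builds the multivariable logistic model by forcing in variables that pass univariate screening or are judged clinically relevant. The Abstract names echocardiographic and angiographic markers among the possible predictors.

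**Timing.** Under Data collection and study procedures, echocardiography "will be performed within 24 hours from admission". Angiography belongs to the AMI work-up. Troponin and NT-proBNP are recorded on admission and at peak. Lp(a), the apolipoproteins, IL-6 and suPAR are admission values.

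**Discussion of imaging.** The Discussion raises as a potential criticism that "differences in imaging parameters between patients with and without SMuRFs are likely to be the consequence of AMI rather than a predictive parameter". It answers that the main objective is to find associations with SMuRF-less status, "which should be tested in future larger trials for their predictive value".

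**Population and outcome.** Under Study design and population, every participant is hospitalised with AMI. The two groups are SMuRF-less patients and patients with at least one SMuRF.

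**The concern.** A tool that recognises risk before an AMI needs inputs that describe the person before the AMI. Here many candidate inputs are taken after onset and may be altered by the infarct or by delay in treating it. The Discussion itself suggests longer time to reperfusion in SMuRF-less patients as a possible reason for worse prognosis. Such delay could plausibly shift troponin, strain and myocardial work, and so separate the groups without saying anything about earlier risk. Because univariate significance is enough for entry to the multivariable model, these markers could enter and raise the ROC area.

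At stake is how the final model is read. An AUC obtained in this cohort could be presented as evidence for a risk-stratification tool when it measures something else.

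**Working it through.** The conflict is one of purpose, timing and outcome. No figure in the article sizes it, so the numerical examples below use assumed values and show only direction and order of magnitude.

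**Step 1. What the plan's own figure refers to.** The sample size takes 15% SMuRF-less prevalence among AMIs and about 75 SMuRF-less patients: 75 / 0.15 = 500, which matches the stated total. The target odds ratio of 2 is therefore for SMuRF-less status among AMI patients. It is not for AMI against no AMI.

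**Step 2. Inputs against intended use.**

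| Candidate inputs | When measured (Data collection) | Describes the pre-AMI state? |
|---|---|---|
| Demographics, history, medication, socioeconomic data | Recorded in hospital, about the past | Yes |
| SF-36 | In hospital, about quality of life before the AMI | Yes, by recall |
| IPAQ activity | Completed before discharge | Yes, if answered for the pre-AMI period |
| Lp(a), ApoB, ApoA1 | On admission | Only by assumption |
| Troponin, NT-proBNP | Admission and peak | No |
| Echo, strain, myocardial work | Within 24 h of admission | May be altered by the AMI |
| Angiography, SYNTAX | AMI work-up | Not obtained before the AMI |

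**Step 3. Effect of a marker changed by the AMI.** Assume a normal marker with equal variances. Assume also that the AMI shifts it by *d* SD in one group only, and that before the event it is unrelated to AMI risk. Within the cohort, AUC = Φ(*d*/√2):

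- *d* = 0.2: Φ(0.141) = 0.56
- *d* = 0.5: Φ(0.354) = 0.64
- *d* = 0.8: Φ(0.566) = 0.71

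For predicting AMI beforehand, the AUC is 0.50 in each case.

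**Step 4. Does removing such markers suffice?** Let a factor have population prevalence *p* in both groups, and relative risk of AMI RR_A in SMuRF-less people and RR_B in people with SMuRFs. Among AMI patients the odds of the factor are *p*·RR/(1 − *p*), so the within-AMI odds ratio is RR_A/RR_B. With *p* = 0.20 (assumed):

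- RR_A = 3, RR_B = 3: odds 0.75 and 0.75, odds ratio 1.0. A factor that triples risk in SMuRF-less people is invisible.
- RR_A = 1, RR_B = 0.5: odds 0.25 and 0.125, odds ratio 2.0. A factor with no effect in SMuRF-less people reaches the plan's target odds ratio.

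Restricting inputs to pre-AMI variables is therefore necessary for the stated goal but not sufficient. Without AMI-free SMuRF-less comparators, the models discriminate between two kinds of AMI patient.

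**The case against.** The strongest reply is that the primary outcome is a comparison of the two groups, and that the Discussion expressly narrows the main objective to association and leaves predictive value to later trials. For describing a phenotype, echo and angiography are legitimate inputs. The risk tool is only an ultimate goal. The label given to the ROC-evaluated models is clinical-laboratory, which might mean that imaging is left out. The exact candidate list may stand in a fuller document.

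Much of this stands. The group comparison is not affected, and using imaging for description is sound. But the article itself states the classes of input, the outcome and the purpose, and these conflict, so the point does not rest on a missing detail. The label follows directly on a sentence that lists imaging among the inputs, so the place of imaging in the final models is unclear. If imaging is excluded, laboratory values taken during the AMI remain.

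Two stronger readings are not supported:

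- A reader might infer that the protocol concedes that all post-onset variables are consequences of the AMI. The Discussion speaks of imaging only, and as a potential criticism. For troponin and NT-proBNP the argument rests on when they are measured.
- A reader might infer that these quantities have no pre-event value. Strain, diastolic measures, NT-proBNP and coronary stenosis can be assessed in people without an AMI. The point is that this study measures them after onset.

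**Conclusion.** The concern holds in this form: the planned models and their ROC curves cannot support a claim to recognise SMuRF-less people at high risk of AMI. There are two reasons. Inputs taken during the AMI may reflect the event, and the outcome is SMuRF-less status among people who all have an AMI. The Discussion's retreat to association was not carried through to the Background goal or the Statistical analysis section.

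The size cannot be taken from the documents. The AUCs of 0.56 to 0.71 against 0.50, and the odds ratios of 1.0 and 2.0, rest on assumed shifts, prevalence and relative risks, and they illustrate the mechanism only. It would go too far to say that the AUC will be inflated by a known amount, or that dropping post-onset variables would by itself yield a valid risk model. The primary group comparison and the prognosis analyses are untouched. The change is worth making before the models are fitted.

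**What to change.** In the Statistical analysis section, fit and report two models separately:

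1. A model restricted to variables fixed or knowable before the AMI: demographics, history, socioeconomic data, physical activity and the pre-AMI SF-36. Lp(a) and apolipoproteins enter only under a stated assumption that admission values reflect pre-AMI levels.
2. A descriptive phenotype model that may add acute biomarkers, echocardiography and SYNTAX. State explicitly whether imaging is included.

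State for both models that the ROC curve measures discrimination of SMuRF-less status among AMI patients and not AMI risk. Reword the goal in the Background and at the opening of the Discussion as phenotyping that generates candidate predictors, to be tested in cohorts with AMI-free SMuRF-less comparators.

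Cost: one extra model run and some rewording, with no new data. The first model will probably show a lower AUC, and the stated goal becomes more modest.

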### Statistical analysis

Clinical parametersc laboratory findings and imaging indices of interest will be compared among patients with and without SMuRFs to phenotypically characterize the SMuRF-less group, and identify any particular associations of these biomarkers with the SMuRF-less status. Subsequently, univariate logistic regression analysis will be performed to identify independent predictors of SMuRF-less AMIs. A multivariate logistic regression model will be constructed by forcing univariably significant and clinically relevant variables into the multivariable model. The G*Power software was utilized by a specialist statistician in order to calculate the sample size required to derive statistical significance. It was estimated that to detect an odds ratio > 2 with a prevalence of 15% of SMuRF-less status among AMIs, approximately 75 SMuRF-less patients will be required (with a probability for Type I error: 0.80, and statistical significance level: 0.05). Therefore, 500 patients (with and without SMuRFs) will be included in the present study. An odds ratio > 2 will be interpreted as a prediction of a 2-fold higher probability of having SMuRF-less AMI than an AMI attributed to SMuRFs.

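### Prediction models are to be judged by ROC curves, with no optimism correction or calibration described, although predictors are selected on the same 500 patients with about 75 SMuRF-less cases

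*Protocol article*

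**What the plan says.** All of this is in the protocol article, mainly under Statistical analysis.

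- **Size.** The calculation is made "to detect an odds ratio > 2 with a prevalence of 15% of SMuRF-less status among AMIs, approximately 75 SMuRF-less patients will be required", and it concludes: "Therefore, 500 patients (with and without SMuRFs) will be included in the present study".
- **Regression.** The multivariable logistic model is built by "forcing univariably significant and clinically relevant variables into the multivariable model".
- **Machine learning.** The plan is that "in order to identify the optimal combination of epidemiological, clinical, laboratory and imaging biomarkers associated with SMuRF-less AMIs, supervised machine learning algorithms will be used". No algorithm is named.
- **Evaluation.** The next sentence reads: "The resulting clinical-laboratory prediction models will be evaluated with Receiver Operating Characteristic (ROC) curves".

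Elsewhere, the last paragraph of the Background makes a risk-stratification model the study's final aim, and the opening of the Discussion repeats it. Under Data collection and study procedures, the primary outcome is defined as a comparison of parameters between the two groups. The Discussion of imaging biomarkers leaves predictive value to later, larger trials. Resampling, a holdout sample, optimism correction, penalisation and calibration are not mentioned anywhere in the article.

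**The concern.** A model is fitted so as to separate the cases and non-cases in its own data. A ROC curve from those data therefore credits the model with chance differences it was free to exploit. The bias grows as cases become fewer and candidates more numerous, and it grows again when the same data choose the predictors or tune the learner. All of these conditions hold here. The sample size was also derived for a single odds ratio of 2, not for developing a model.

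A ROC curve depends only on how patients are ranked. It cannot show whether predicted probabilities are right, which a risk-stratification tool needs.

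At stake is the AUC reported for the selected biomarker combination. If it is the apparent AUC, it does not estimate performance in other patients, and a chance combination could be carried forward on the strength of it.

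**Working it through.** **The plan's own figures.** Expected SMuRF-less patients: 0.15 × 500 = 75, as stated. The sentence labels 0.80 as a Type I error ("with a probability for Type I error: 0.80, and statistical significance level: 0.05"); I read it as power, with two-sided alpha 0.05. For a binary predictor with prevalence p0 in the SMuRF group and odds ratio 2:

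- p1 = 2·o/(1 + 2·o), where o = p0/(1 − p0)
- k = 85/15 and p̄ = (p1 + k·p0)/(1 + k)
- cases = [1.96·√((1 + 1/k)·p̄(1 − p̄)) + 0.842·√(p1(1 − p1) + p0(1 − p0)/k)]² / (p1 − p0)²

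p0 is not stated. At p0 = 0.40 the formula gives 77 cases (total 77/0.15, rounded up to 514), close to 75 of 500. At 0.30 or 0.50 it gives 81, at 0.20 it gives 96, and at 0.10 it gives 154. So 75 is reproducible as the number for one predictor, and I take it as the case count.

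**Candidates (assumption).** No count is given. About 39 items are named one by one under Data collection and study procedures. Demographics, history, medication, blood count, biochemistry and coagulation come on top as unlisted groups. Fifty is a fair working value, and I show 30 to 100. Cases per candidate: 75/30 = 2.5, 75/50 = 1.5, 75/100 = 0.75.

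**Simulation.** Each dataset has 75 cases, 425 non-cases and independent standard normal predictors unrelated to outcome, so the true AUC is 0.50. There are 200 datasets per setting. Each fitted model is scored on its own data (apparent) and on 2,000 new patients. The screen is a t-test at p<0.05; if nothing passes, the AUC is set to 0.50.

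| Candidates | Apparent AUC, unscreened logistic (95% range) | Apparent AUC, screened logistic (95% range) | New data |
|---|---|---|---|
| 30 | 0.69 (0.64–0.74) | 0.58 (0.50–0.67) | 0.50 |
| 50 | 0.74 (0.69–0.78) | 0.61 (0.50–0.70) | 0.50 |
| 70 | 0.79 (0.75–0.83) | 0.65 (0.50–0.72) | 0.50 |
| 100 | 0.85 (0.81–0.89) | 0.68 (0.60–0.76) | 0.50 |

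Two further settings with 50 candidates:

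- Screen plus forced clinical variables, which is closest to the regression described: 0.64 with 5 forced and 0.66 with 10 forced, upper limit 0.72 in both; new data 0.50.
- Boosted stumps, 100 rounds, learning rate 0.1, 40 datasets: 0.91 (0.89–0.93); new data about 0.50.

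**Hand check of the unscreened column.** With P noise predictors the expected R² is P/499. The apparent squared distance between groups is D² = [500 × 498/(75 × 425)] × R²/(1 − R²) = 7.81 × R²/(1 − R²), and AUC ≈ Φ(D/√2). For P = 50: R² = 0.100, D² = 0.870, D = 0.933, and Φ(0.660) = 0.745. For P = 30: D² = 0.500 and AUC = 0.69. Both agree with the table.

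**Does the remedy work?** Ten-fold cross-validation with the screen repeated in each fold (50 noise candidates, 60 datasets) gives a mean AUC of 0.50 for both the unscreened and the screened logistic model. It identifies the useless model as useless.

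**The case against.** The article is condensed, and resampling and tuning schemes are commonly left to an analysis plan, which is not shown here. A ROC curve can be drawn from cross-validated or bootstrap-corrected predictions, so the evaluation sentence is compatible with sound practice. A reader might infer that ROC curves are the only evaluation and that there will be no internal validation. The text does not say so: that reading rests on silence, and I do not assert it. What remains is that the article does fix an evaluation method, and as worded that method is not sufficient for models selected on the same data.

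A reader might also infer that a useless model is bound to look good. For the regression route described, that is too strong. With 50 noise candidates the average is about 0.61, or 0.64 to 0.66 with forced variables: inflated, but still weak discrimination. The high values come from an unscreened model, which the article does not describe, and from one learner at one setting, while the article names no algorithm. The ROC sentence directly follows the machine-learning step, though, so the learner is the more relevant case, and how large its inflation is depends on a choice not yet stated.

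It would likewise be wrong to conclude that the study cannot tell a phenotype from noise. The primary comparisons use chi-square, t and Mann-Whitney tests and need no AUC.

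Finally, the Discussion leaves predictive value to future trials. That limits the claim made for the model, but it does not make this study's own AUC unbiased.

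**Conclusion.** The point holds as a weakness in the stated evaluation of the prediction models, and I class it as a cheap improvement. If the ROC curve is computed on the development data, an AUC that should be 0.50 would average 0.58 to 0.68 after univariable screening and 0.69 to 0.85 without it, over 30 to 100 candidates. For a flexible learner with 50 candidates it could be about 0.91.

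The result rests on the article's figure of about 75 cases in 500, on an assumed candidate count, and on independent normal predictors. Correlation among the real biomarkers would reduce the inflation somewhat. The consequence is confined to the risk-model aim stated in the Background and Discussion.

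**What to change.** Replace the sentence on ROC evaluation with:

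> Discrimination (AUC with 95% CI) and calibration (slope, intercept) of the prediction models will be estimated with bootstrap optimism correction or repeated nested cross-validation, with variable screening and tuning repeated inside every resample; apparent AUC will not be presented as model performance.

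If the full protocol or analysis plan already specifies this, a reference to it is enough. The cost is computing time and a lower reported AUC. No holdout sample is needed, so no patients are lost to model building, and no new data have to be collected.
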